|                    |                                                                                                                                                             | Somewhat happy                                         |  | 4  |  |
|                    |                                                                                                                                                             | Very happy                                             |  | 5  |  |
|                    |                                                                                                                                                             | Don't know                                             |  | 99 |  |
| 4.2                | What are the main reasons you choose to come to this facility, as opposed to another facility, for care?                                                    | This facility is closest to me                         |  | 1  |  |
|                    |                                                                                                                                                             | This facility has less wait time than other facilities |  | 2  |  |
|                    |                                                                                                                                                             | This facility is stocked/usually stocked with drugs    |  | 3  |  |
|                    |                                                                                                                                                             | I like the healthcare workers at this facility         |  | 4  |  |
|                    |                                                                                                                                                             | I have friends who come to the facility                |  | 5  |  |
|                    |                                                                                                                                                             | I like the counseling sessions at the facility         |  | 6  |  |
|                    |                                                                                                                                                             | I like the fact that families come on the same day     |  | 7  |  |
|                    |                                                                                                                                                             | Other (specify): _____                                 |  | 98 |  |

|     |                                                                                                                                                                                                   |                                                                                                           |  |    |  |
|-----|---------------------------------------------------------------------------------------------------------------------------------------------------------------------------------------------------|-----------------------------------------------------------------------------------------------------------|--|----|--|
| 4.3 | What are the factors that you think work well in this clinic?                                                                                                                                     | List most common                                                                                          |  |    |  |
| 4.4 | Do you have any concerns about getting 3 months of ART drugs at the same time?

Choose all that apply (Do not prompt or mention options – allow the respondent to answer directly)   | Losing medication                                                                                         |  | 1  |  |
|     |                                                                                                                                                                                                   | Forgetting to come back after 3 months                                                                    |  | 2  |  |
|     |                                                                                                                                                                                                   | Facility will run out of drugs if everyone gets 3 months                                                  |  | 3  |  |
|     |                                                                                                                                                                                                   | Not having a safe place to store drugs                                                                    |  | 4  |  |
|     |                                                                                                                                                                                                   | Not being able to see a doctor or nurse for 3 months                                                      |  | 5  |  |
|     |                                                                                                                                                                                                   | Other (specify):
_____                                                                                 |  | 98 |  |
|     |                                                                                                                                                                                                   | Don't know                                                                                                |  | 99 |  |
| 4.5 | Do you prefer to receive 3 or more months of ART drugs at a time?                                                                                                                                 | Yes, I prefer to receive three or more months of drugs at a time                                          |  | 0  |  |
|     |                                                                                                                                                                                                   | No, I prefer to receive a smaller amount of drugs at a time                                               |  | 1  |  |
|     |                                                                                                                                                                                                   | Don't know                                                                                                |  | 99 |  |
| 4.6 | Are there any reasons why it is good to receive 3 months of ART drugs at a time?

Choose all that apply (Do not prompt or mention options – allow the respondent to answer directly) | Not having to come back to clinic as often                                                                |  | 1  |  |
|     |                                                                                                                                                                                                   | Knowing that I have the medication I need for at least 3 months                                           |  | 2  |  |
|     |                                                                                                                                                                                                   | Not having to wait in line as long at the pharmacy because there are not as many patients coming each day |  | 3  |  |
|     |                                                                                                                                                                                                   | Other (specify):
_____                                                                                 |  | 98 |  |
|     |                                                                                                                                                                                                   | Don't know                                                                                                |  | 99 |  |

**QUESTIONS TO BE USED IN ENDLINE, POST-INTERVENTION SURVEY ONLY, ONLY FOR THOSE PATIENTS IN FACILITIES THAT RECEIVED AN INTERVENTION (IN ADDITION TO ABOVE)**

|     |                                                                                                       |            |  |    |             |
|-----|-------------------------------------------------------------------------------------------------------|------------|--|----|-------------|
| 4.7 | Have there been any changes in the care that you have received at this facility in the last 4 months? | No         |  | 0  | SKIP TO 4.6 |
|     |                                                                                                       | Yes        |  | 1  |             |
|     |                                                                                                       | Don't know |  | 99 | SKIP TO 4.6 |
| 4.8 | Please describe any changes that have happened in the care that you receive?                          |            |  |    |             |
| 4.9 | Did you receive ART drugs during this                                                                 | No         |  | 0  | SKIP        |

|      |                                                                                                                                              |                        |  |    |              |
|------|----------------------------------------------------------------------------------------------------------------------------------------------|------------------------|--|----|--------------|
|      | visit?                                                                                                                                       |                        |  |    | TO 4.8       |
|      |                                                                                                                                              | Yes                    |  | 1  |              |
|      |                                                                                                                                              | Don't know             |  | 99 | SKIP TO 4.8  |
| 4.10 | How many months of ART drugs did you receive?                                                                                                | Less than one month    |  | 0  | SKIP TO 4.10 |
|      |                                                                                                                                              | One month              |  | 1  |              |
|      |                                                                                                                                              | Two months             |  | 2  |              |
|      |                                                                                                                                              | Three months           |  | 3  |              |
|      |                                                                                                                                              | More than three months |  | 4  |              |
|      |                                                                                                                                              | Don't know             |  | 99 | SKIP TO 4.10 |
| 4.11 | Have you ever received 3 or more months of ART drugs during one visit in the past?                                                           | No                     |  | 0  |              |
|      |                                                                                                                                              | Yes                    |  | 1  |              |
|      |                                                                                                                                              | Don't know             |  | 99 |              |
| 4.12 | During your visit today, did a doctor, nurse or pharmacist talk to you about the importance of taking your ARTs on schedule?                 | No                     |  | 0  |              |
|      |                                                                                                                                              | Yes                    |  | 1  |              |
|      |                                                                                                                                              | Don't know             |  | 99 |              |
| 4.13 | Are you aware that your clinic is making an effort to improve the efficiency of the clinic and give you 3 month rather than shorter refills? | No                     |  | 0  |              |
|      |                                                                                                                                              | Yes                    |  | 1  |              |
| 4.14 | How does receiving a 3 month rather than a shorter refill change your experience in receiving care at this facility?                         |                        |  |    |              |

[figure not shown]

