## Primary Outcome

The primary outcome is the proportion of stable ART patients receiving 3-month refills, defined as:

The number of stable patients given a 3-month refill in the previous month divided by the total number of stable patients seen in the last month.

Stable patients are defined as:

A patient active in ART care for more than 6 months and on first-line treatment as outlined in the Zambia Consolidated Guidelines (includes the following combinations **(1)** TDF + XTC + EFV, **(2)** TDF + XTC + LPV-r, **(3)** TDF + XTC + ATV-r, **(4)** TDF + XTC + NVP+, **(5)** AZT + 3TC + LPV-r, **(6)** ABC + 3TC + LPV-r, **(7)** ABC + 3TC + EFV).

Secondary outcomes include:

- Patient wait times based on the daily average wait time from entry into the clinic to medication delivery
- Compliance to quality improvement standard operating procedures
- Patient satisfaction and perceptions of quality of care
- Patient experiences with transition to multi-month refills
- Provider perspectives on process of implementing clinical efficiency and supply chain interviews and on barriers or challenges to providing multi-month refills
- Patient and provider perceptions on reliability of supply chain

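### Exit-interview item 4.13 is leading and double-barrelled and comes directly before 4.14, so awareness may be misreported and answers on the refill change may be influenced

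*Combined protocol and SAP*

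**What the plan says.** The last part of the Patient Exit Interview (Annex 7), items 4.7 to 4.14, is for the endline survey and "ONLY FOR THOSE PATIENTS IN FACILITIES THAT RECEIVED AN INTERVENTION (IN ADDITION TO ABOVE").

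Item 4.13 asks, in one sentence, whether the patient is aware that "your clinic is making an effort to improve the efficiency of the clinic and give you 3 month rather than shorter refills". Its only codes are No (0) and Yes (1). Item 4.14, the last on the form, is open text: "How does receiving a 3 month rather than a shorter refill change your experience in receiving care at this facility".

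Section 6.1.3 lists "Patient experiences with transition to multi-month refills" as a secondary outcome, and section 4 lists it among the secondary aims. Patients' awareness of the programme is neither an aim nor an outcome, and sections 6.5 and 6.5.1 describe no analysis of it.

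Earlier in the form, items 4.4 to 4.6 ask about concerns over 3-month supplies, the patient's preference and possible advantages. Items 4.7 ("Have there been any changes in the care that you have received at this facility in the last 4 months") and 4.8 ("Please describe any changes that have happened in the care that you receive") ask about change without naming the programme. Items 4.9 to 4.11 ask what drugs were received now and in the past.

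**The concern.** A question that supplies the fact it is meant to measure invites agreement. A Yes to 4.13 does not separate a patient who knew from one who has just been told. Because two topics share one answer, a patient who noticed only one of them has no correct reply, and no later analysis can tell the two apart.

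The order matters as well. The patient hears that the clinic is making an effort on his or her behalf and is then asked, in an interview on leaving that clinic, how a 3-month refill changes the experience. Section 6.5.4 says the results go to the Ministry of Health to inform scale-up. This block has no baseline or control answers, so nothing in the data could reveal or cancel an influence on 4.14. Wording and order are the only protection for this outcome.

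**Working it through.** The plan states no figure on this point, so the check is mainly a reading of wording, codes, order and routing.

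1. **Leading wording.** The clinic's effort is asserted inside 4.13 and the patient is asked only to confirm knowing it. Items 4.4 and 4.6 take the opposite approach: the interviewer is told not to prompt or mention the answer options.
2. **Two topics, one answer.** The second half, "improve the efficiency of the clinic and give you 3 month rather than shorter refills", joins efficiency and refill length with 'and' under one No/Yes.
3. **Codes.** Items 4.11 and 4.12 have Don't know (99). Item 4.13 does not.
4. **Order and routing.** As printed, no skip passes over 4.13, and 4.14 follows it directly. The skips at 4.7, 4.9 and 4.10 point to 4.6, 4.8 and 4.10, that is, backwards or to the item itself, so they need renumbering in any case.
5. **What 4.14 assumes.** It presupposes a 3-month refill. Item 4.10 allows answers of less than one, one or two months, and no usable skip keeps those patients out of 4.14, so some answers would be hypothetical.
6. **Reach.** There are 16 facilities in matched pairs with one of each pair assigned to the intervention (sections 6.1 and 6.1.1), so 16 / 2 = 8 facilities use the block.

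**Direction of error in recorded awareness.** Let p be the true share aware of both topics, a the share of the rest who say Yes, and b the share of the aware who say No. Then

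recorded Yes = p(1 − b) + (1 − p)a,

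which exceeds p only when (1 − p)a > pb. The documents give none of these rates. All values below are assumptions.

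| p | a | b | Recorded Yes |
|---|---|---|---|
| 30% | 10% | 0 | 0.30 + 0.70 × 0.10 = 37% |
| 30% | 30% | 0 | 0.30 + 0.70 × 0.30 = 51% |
| 60% | 10% | 0 | 0.60 + 0.40 × 0.10 = 64% |
| 60% | 30% | 0 | 0.60 + 0.40 × 0.30 = 72% |
| 60% | 10% | 20% | 0.60 × 0.80 + 0.40 × 0.10 = 52% |

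The first four rows overstate awareness by 4 to 21 percentage points. The last understates it by 8. The table shows that the direction depends on the unknown rates; it does not estimate the error. No comparable calculation is possible for 4.14, which is open text.

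**The case against.** The strongest reply is that little rests on these items. Awareness is not an outcome, and no analysis of 4.13 is planned. The primary outcome comes from ART register and pharmacy records, wait times come from the patient flow form, and the satisfaction rating at 4.1 is taken before 4.13. The block is used in one arm only, so it cannot bias a comparison between arms. All of this stands, and it sets the severity.

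The second reply is that 4.13 is not the only cue. Items 4.4 to 4.6 have already raised 3-month supplies, concerns first and advantages last. Items 4.10 and 4.11 ask about receipt. Patients hear an explanation of the study at consent, and its text is not in the review copy. Some courtesy towards the clinic would be expected anyway, and 4.14 itself uses a neutral verb. So what 4.13 adds cannot be isolated. It remains the only item on the form that credits the clinic with an effort for the patient's benefit, and it sits immediately before the item on experience.

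The third reply is that 4.7 and 4.8 record change before the programme is named. That is a real but partial safeguard, because they ask about care in general and not about the move to longer refills.

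A reader might go further and infer that awareness is overstated and that the answers to 4.14 are pushed towards benefit. The documents support neither as a fact. The double wording can also move a partly aware patient to No, and nothing in the plan shows which way, or how far, the open answers would shift.

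**Conclusion.** The point holds as a minor weakness of the questionnaire. Item 4.13 is leading, double-barrelled and without a Don't know code, and it directly precedes the only item worded as experience of the refill change. Awareness may be misreported, more likely upward. Answers to 4.14 may be influenced. Neither effect can be sized.

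The consequence is confined to a descriptive secondary outcome with no comparator, at the 8 intervention facilities. This assumes that the form is administered in its printed order and that no separate interviewer instruction changes the routing; the documents show none.

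**What to change.** - **Move 4.14** ahead of any statement of programme intent. Ask it only of patients who report a refill of three or more months at 4.10 or 4.11, and add a neutral prompt: better, worse or no change.
- **Replace 4.13** with two separate items that do not state the aim, for example: 'Have you heard of any change in how this clinic is run?' and 'Have you heard of any change in how many months of ART drugs patients are given?' Code each No / Yes / Don't know. Each item should keep to one topic; adding visit length to the first would repeat the fault.
- **Report the two items as prompted awareness**, since earlier items, and 4.14 once moved, already mention 3-month refills. Use 4.7 and 4.8 for change that patients report unprompted.
- **Correct the skip targets** in the block in the same edit.

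The cost is about one extra question per interview and a notice to the IRB, which approves the questionnaires (section 6.3.4). The block is used only at endline, so no baseline data are affected. Once the endline interviews are done, the weakness cannot be repaired.
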